**Methodology and Study Design:**

The effectiveness of the project will be measured in terms of the impact of the proposed interventions on the stunting and micronutrient deficiency prevalences in the target group (children and mothers). Given the conditions of project implementation, a quasi-experimental “double difference” design would be appropriate to assess the impact of the intervention. We propose to compare the intervention and non-intervention (control) groups before (first difference) and after the intervention (second difference).

Then, the operational implementation of the research comprises a baseline and end line surveys. In addition, a nested cluster randomized controlled trial will be implemented to track the evolution of key variables related to the quality of intervention delivery and intermediate nutrition outcomes. The control clusters will receive routine public and private health services available in the area. The overall research design is shown in Figure 1.

**Figure 1: Overall research design**

[figure not shown]

To ensure the robustness of this program a baseline and endline surveyswith a nested cluster randomized control trial to evaluate the programme in terms of nutrition and other core indicators is required. Therefore Division of Women & Child Health Aga Khan University proposes two separate cross sectional surveys which will be conducted in the target union councils of District Thatta-Sajawal to address the objectives of impact assessment of stunting prevention project. A baseline cross sectional survey will be conducted to provide benchmark indicators and frame work for the implementation of program. A structured questionnaire will be used to accomplish this information. At the end of the program an end line cross sectional survey will be conducted to assess the impact of the program, where the nutrition and other core indicators will be compared for pre and post intervention change.

**Study site**

This study will be conducted in 29 Union councils of districts Thatta and Sajawal of Sindh Province. The LHW catchment area of 29 targeted union councils of these districts will be in the intervention group, while remaining uncovered area of these union councils will be in control group. The UC wise details of LHWs, total population as well as covered and uncovered population are attached in annex I.

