**Children 0-59 months**

- Immunization
- Treatment of common diseases, including malaria prevention
- Treatment of acutely malnourished children: inpatient and outpatient care

The above activities are being delivered by the health sector and the LHWs. In addition MERLIN through its EU funded project will reinforce all the behavior change, community outreach and CMAM activities in most of the UCs in the district.

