**Training of the LHWs**

The LHWs provincial and district level staff, health sector staff involved in the project and the LHWs and supervisors will attend a two days training before starting the distribution of food supplements. A cascade training approach will be followed, first training Master trainers for each health facility, followed by the LHWs training. Main topics for the trainings are: the benefits and use of the products, the delivery strategy and reporting. A brief refreshment session on IYCF and maternal nutrition will be also included (it is assumed that LHWs are already trained in these topics).

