**Delivery of IYCF and PLW nutrition education**

Messages will be delivered by the LHWs at the household visits. During the monthly household visit, the LHWs will weight all 6-23 months children and register the weight in the growth monitoring chart. Nutrition counseling will be then provided according to child´s age and direction of the weight monitoring chart. More attention will be given to those children that lost weight or not gained weight; inquiring on the possible causes and providing advice on corrective measures related to improved child feeding and care practices.

Other complementary activities such all preventive health is being implemented by other stakeholders, as mentioned above.

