**Objectives of impact assessment of Stunting Prevention Project by AKU**

The broad objectives of the research component of the project are:

1. To assess the effectiveness of the food/nutrient -based interventions on reduction of stunting among children under two.
2. To assess the effectiveness of the food/nutrient-based interventions on reducing stunting and micronutrient deficiencies in children 6-59 months.
3. To assess the effectiveness of the food/nutrient-based interventions on reduction of wasting and anemia in pregnant and lactating women and an impact on the birth outcome (reduce low birth weight),
4. To assess the design and operational factors at the different stages of the programme cycle that may have affected the outcome.
5. To determine unintended consequences of the interventions, both positive and negative.
6. To determine cost-effectiveness.
7. To provide recommendations for improved programme design and evaluation.
8. To know the optimal length of preventive intervention.
9. To compare the use of specialized nutritious foods over other interventions, such as conditional cash transfers for stunting prevention.

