**Cost Effectiveness Analysis**

Cost effectiveness analysis will run through the full three years of the program. For our analysis we will have 2 arms whose cost effectiveness will be compared: Arm 1: food based and preventive health interventions; Arm 2: preventive health interventions only. The time frame for both will be three years of intervention

To be able to assess the cost effectiveness of the intervention and control arms current, we will compare interventions with a scenario of doing nothing to improve child health. Incremental cost effectiveness ratios will be computed for each arm by calculating the incremental improvement over Do Nothing scenario.

A sensitivity analysis will be carried out to report results with or without 3% discounting for DALYs and using cost inputs for foreign prepared versus locally prepared supplements.

*Cost Calculation:* Unit costs for provision of food supplements and for delivery of preventive health measures will be developed based on programmatic records. A record of program inputs and costs will be maintained during the length of the program and verified by an external accountant. 2013 as the base year will be kept as the base year with costs converted to 2013 purchasing power parity to remove the effect of inflation. All costs will be summarized in US dollars and future costs discounted at 3%.

*Effect Calculation*: Percent reduction in stunting will be taken as the effect outcome. Efficacy will be obtained through Before After household survey. Changes in linear growth will also be calculated.

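### The cost-effectiveness section treats the survey arms as differing only by food, but the survey contrasts LHW-covered with uncovered areas and cannot isolate the supplements

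*Protocol*

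**What the plan says.** Under Study site, the areas that LHWs serve within the 29 union councils form the treated survey group. For the comparison group the text reads: "while remaining uncovered area of these union councils will be in control group". Under Methodology and Study Design, these groups are compared by a quasi-experimental double difference with one baseline and one endline survey; the stated target is the effect of the project and its proposed interventions. The first research objective is "To assess the effectiveness of the food/nutrient -based interventions on reduction of stunting among children under two".

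The project delivers more than supplements in covered areas. The WFP Intervention Modalities section pairs the supplements with behaviour change communication and plans formative research to tailor the messages to the district. On feeding and maternal nutrition education, "Messages will be delivered by the LHWs at the household visits". LHWs and their supervisors "will attend a two days training before starting the distribution of food supplements", which includes a short refresher on infant feeding and maternal nutrition. Product education accompanies each distribution. On the preventive services listed as complementary interventions, "The above activities are being delivered by the health sector and the LHWs".

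The Cost Effectiveness Analysis section then defines two arms. Arm 1 is food plus preventive health, and "Arm 2: preventive health interventions only". It takes efficacy from the before-after household survey.

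**The concern.** As labelled in the Cost Effectiveness Analysis section, the two arms share preventive health care and differ by food alone. The survey that is to supply the effect does not make that comparison. Its control areas have no LHW, so they lack the LHW-delivered share of preventive care and all of the counselling that the project adds through LHWs. No survey group receives the project's counselling without the supplements.

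The double difference removes a stable gap between the areas. It does not remove anything that starts, intensifies or trends differently on one side after baseline. If the plan is followed as written, everything in that category is credited to food, both in the effect and in the cost per unit of effect. The protocol says the endline findings will inform the decision to scale up. A programme that copied the food component but not the counselling could then fall short of the reported effect.

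**Working it through.** **Inputs.** Baseline stunting is 49% and the planned effect is a 10% reduction (Sample size and design for Baseline and End line Surveys). The text does not say whether the 10% is relative or absolute, so the effect is either 0.10 × 49 = 4.9 points or 10 points. The protocol gives no figure for the contribution of the non-food components, so the shares below are assumptions that only illustrate.

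**Step 1: what cancels.** Let I and C be stunting prevalence in covered and uncovered areas, with 0 for baseline and 1 for endline.

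DD = (I1 − I0) − (C1 − C0)

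Take I0 = 49.0% and I1 = 44.1%, and let uncovered areas stand g points higher in both rounds.

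| Standing gap g | Endline-only difference, (49 + g) − 44.1 | Double difference (size of reduction) |
|---|---|---|
| 0 | 4.9 | 4.9 |
| 3 | 7.9 | 4.9 |
| 6 | 10.9 | 4.9 |

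The gap drops out. The LHW programme is an existing platform (Project Delivery Mechanism) and household visits at least monthly are already routine (Supplementary products delivery), so the stable part of LHW care is removed under parallel trends.

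**Step 2: what does not cancel.** Write the size of the double difference as

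DD = F + B + T

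where F is the effect of the supplements, B that of the other components the project adds or strengthens through LHWs (including any interaction with the supplements), and T the difference in background trend. The survey gives one equation for three unknowns. T cannot be checked with one round before and one after. B cannot be separated by design because F and B are switched on in the same areas.

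**Step 3: illustration.** If B + T make up a share s of DD, then F = DD × (1 − s).

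| Assumed s | F if DD = 4.9 points | F if DD = 10 points |
|---|---|---|
| 0% | 4.9 | 10.0 |
| 25% | 3.7 | 7.5 |
| 50% | 2.5 | 5.0 |
| 75% | 1.2 | 2.5 |
| 100% | 0.0 | 0.0 |

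The observed result is the same in every row of a column. T can have either sign, so the food-only effect could also exceed DD.

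**Step 4: the sections side by side.**

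| | Cost-effectiveness label | What the survey supplies |
|---|---|---|
| Intervention | Food plus preventive health | Supplements, LHW-delivered education and counselling, existing LHW services, health-sector care |
| Comparison | Preventive health only | Routine services without an LHW |
| Difference | Food | Everything new or trending differently in covered areas |

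If supplement costs alone were set against the whole survey effect, the cost per point would be too low by the factor 1 − s. At s = 50%, for example, cost ÷ 4.9 would be reported where cost ÷ 2.45 applies.

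**The case against.** The strongest reply is that the package is largely the declared intervention. The intervention section defines supplements together with behaviour change communication, and the design section measures the project as a whole. The first objective refers to food/nutrient-based interventions, not to supplements alone. For that estimand, counselling is part of treatment and not bias. This stands, and it is why the conflict lies in the Cost Effectiveness Analysis section and not in the survey design itself.

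Three stronger readings are tempting, and the protocol does not support them:

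- A reader might infer that the survey estimates the whole LHW programme against none. It does not, because LHW services that predate the project and stay stable cancel (Step 1).
- A reader might infer that only LHW areas receive the partner organisation's reinforced outreach. The protocol places this in most union councils of the district. The survey controls lie within the same 29 union councils and are not excluded.
- A reader might infer that Arm 2 does not exist in the control areas. Preventive care comes from the health sector as well as from LHWs, and controls keep routine services. Only the LHW-delivered share is missing.

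It is also fair to say that the new non-food part may be modest: the training is mainly about products, delivery and reporting, and its feeding content is a brief refresher. But modest is not zero, and the protocol gives no size. The questionnaires record supplement receipt, LHW contact and communication sessions, so exposure analyses are possible, but they would be observational. Costing each arm against a do-nothing scenario does not help, because the arm labels still decide what the survey effect is attributed to. The nested cluster trial does not fill the gap either: its controls receive routine services, no arm is described as receiving counselling without supplements, and the cost-effectiveness section draws on the survey.

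Choice of covariates is normally left to an analysis plan. The arm definitions and the source of the effect are not: this protocol fixes them.

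**Conclusion.** The point holds in a limited form. The survey can estimate the effect of everything the project adds in LHW-covered areas, provided that covered and uncovered areas would otherwise have followed parallel trends. That suits the stated project evaluation. It does not support the food-only contrast in the Cost Effectiveness Analysis section, so that section and Study site must be reconciled.

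The size of the misattribution is unknown. The 0% to 100% shares show that the food-only effect is not identified; they do not estimate how much of the effect is non-food. The conclusion rests on the arm definitions and on the project adding some LHW-delivered education, both of which the protocol states. It does not depend on any assumed share, nor on whether the planned 10% is relative or absolute.

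**What to change.** 1. **Cost Effectiveness Analysis.** Redefine the arms to match the survey: the project package (supplements plus LHW-delivered behaviour change communication, on top of existing LHW services) in covered areas, versus routine services in uncovered areas. Cost the whole package and take the effect from the double difference. Do not present the ratio or the survey result as the effect of food alone.
2. **Methodology and Study Design, and Study site.** State the survey estimand as the effect of everything the project adds in LHW-covered areas, conditional on parallel trends, and say that two rounds cannot test that condition.
3. **Analysis.** Adjust the double difference for covariates collected in both rounds that the programme is unlikely to change: wealth index, maternal education and distance to the nearest health facility (Outcome Indicators for the survey). Do not adjust for endline food insecurity or programme exposure, which the programme may itself alter. Adjustment makes parallel trends more plausible; it does not verify them.

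No new data are needed. The cost is rewording, one adjusted model, package-level costing and a narrower claim from the survey.

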**Description of Proposed Activities:**

**A: Baseline and End Line surveys**

A cross sectional baseline and endline surveys will be conducted at household level for socio-economic status and nutrition related indicators. The baseline & end line surveys will be completed within three months. Following information will be collected from children under five years of age and pregnant or lactating women where available in selected households.

**Proposed Methodology for Baseline and End line Survey**

**1-Household size, socio-economic, household expenditure, hand washing, exposure to interventions, IYCF, food consumption & diet diversity, and morbidity information**

Household information will be captured from a pregnant woman or mother of under-five children. A structured questionnaire will be used to assess socio-economic status, family size, household expenditures, infant and young child feeding practices; exclusive breastfeeding and complementary feeding status. Additionally data on food intake, food consumption & diet diversity and food insecurities will be collected during baseline and endline surveys. Knowledge, attitudes and practices regarding micronutrients and hand washing practices will also be collected. The quantitative information will include precise energy, exposure to interventions, nutrient and food intakes estimates along with supplementation and fortification details. Apart from the above mentioned information, child’s health status, vaccination history and details of morbidity due to diarrhoea and pneumonia will also be collected in baseline and endline surveys.

**2- Anthropometric measurements, haemoglobin testing and physical examination.**

Height, weight and mid upper arm circumference (MUAC) measurements will be taken for all target population. Children’s ages will be determined from birth certificate, immunization card or other documentation, if available at the time of survey. If no such documentation is available, a local calendar will be used to determine age to the nearest month. Anthropometric indicators of length/height-for-age, weight-for-age and weight-for-length/height will be determined from above mentioned data. Physical examination will be performed of all targeted population to assess the signs of anaemia. In addition to the General examination of children and mother a spot haemoglobin test will also be done using a Hemo cue machine to assess the prevalence of anaemia.

**Sample size and design for Baseline and End line Surveys**

Clearly it would be impossible to conduct an in-depth evaluation of all population in the community based nutrition program. However, the assessment must be robust, scientifically valid and plausible within existing time frames. Therefore a representative sample size has been calculated separately for both baseline & endline surveys and embedded Randomized control trial. Details of both estimations are as under:

Below mentioned formula for sample size estimation for baseline and endline cross sectional surveys were used from MI & CDC manual [6] to calculate the sample size. Prevalence of stunting (49% Sindh) from NNS 2011, 80% power to detect 10% reduction in prevalence of stunting during the three-year implementation of the Stunting Prevention Programme with a significance level of 0.05 was considered for sample size estimation.

[figure not shown]

Assumptions:

- p1 is stunting rate at baseline without intervention at baseline survey =49%
- p2 is estimated stunting rate after intervention at end line survey
- DEFF : The estimated design effect = 1.5
- α : Level of significance (“alpha”), usually 0.05 or 5% (corresponds with 95% confidence interval)
- 1- β: Power, usually 0.8 (80%) Assumed 10% reduction in stunting

For estimating impact of the interventions each group will require 3200 participants. To account for dropouts and data errors, the sample size will increased by 10% giving a new total of 7040 study participants (3520 participants per group). Information will be collected from 4,200 households at baseline and at endline. The study participants from selected households will be pregnant women, lactating women and children under five years. Two stage cluster sampling technique will be used. LHW catchment areas of 29 UCs will be treated as a cluster for intervention group and control group.

All household with pregnant women, lactating mothers and children under five years of age will be eligible for baseline survey. LHW khandan register will be used to identify and select the eligible subjects in intervention clusters where available. A unique identification number will be assign to both children and mothers at the time of recruitment for the baseline survey. Social mapping approach (meeting with community elders, mothers, dais, community midwife, community/social workers etc.) will be used to identify the eligible subjects in control clusters. A list of eligible subjects will be prepared based on social mapping method and households with eligible subjects will be randomly selected for baseline survey.

Similarly all households with pregnant women, lactating mothers and children under five years of age at the time of endline will be eligible for endline cross sectional survey. Eligible subjects will be randomly selected from both intervention and control areas to see the overall impact of intervention on target population.

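### The survey sample size of 3,200 per group does not follow from its stated inputs, and those inputs describe a simple comparison of two rates, not the planned double difference

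*Protocol*

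**What the plan says.** The Protocol, under Sample size and design for Baseline and End line Surveys, claims "80% power to detect 10% reduction in prevalence of stunting" and lists its assumptions: "p1 is stunting rate at baseline without intervention at baseline survey =49" (per cent), "DEFF : The estimated design effect = 1.5", and an alpha of 0.05 that "corresponds with 95% confidence interval". The endline rate p2 is named but given no value, and the text does not say whether the 10% is relative or in percentage points. The formula is a figure that is not shown in the text at hand.

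The result is "For estimating impact of the interventions each group will require 3200 participants". This is raised by 10% to 3,520 per group, 7,040 in total, with 4,200 households visited at baseline and at endline. The section adds: "The study participants from selected households will be pregnant women, lactating women and children under five years".

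The contrast is described in more than one way. Methodology and Study Design calls for a double difference: "We propose to compare the intervention and non-intervention (control) groups before (first difference) and after the intervention (second difference". The text under Figure 1 speaks of comparing indicators before and after the intervention, and Cost Effectiveness Analysis takes its effect from the before-and-after household survey.

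**The concern.** A stated sample size should be recoverable from its stated inputs, and it should be computed for the contrast that will be analysed. Here neither can be confirmed.

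The two rates listed allow for no change in the control group. A double difference combines four estimated prevalences instead of two, so at the same number per cell its variance is about twice as large. If the double difference is the impact estimate, the claimed 80% power may not apply to it, and a null result could be read as programme failure when the survey was simply imprecise. The endpoint behind the sizing is stunting in children, yet the section never says how many of the participants are children.

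**Working it through.** **Inputs.** From the survey sample-size section: p1 = 0.49, a 10% reduction, design effect 1.5, alpha 0.05, power 80%. The wording about a 95% confidence interval implies a two-sided test. p2 is not given, so both readings are tried: 0.441 (relative) and 0.39 (10 points).

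**1. The protocol's figure.** The inflation step is consistent: 3,200 × 1.1 = 3,520, and 2 × 3,520 = 7,040. The 3,200 itself is not reproduced.

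Two proportions, unpooled variance: n = (1.96 + 0.8416)² × [p1(1−p1) + p2(1−p2)] / (p1−p2)², where (1.96 + 0.8416)² = 7.849.

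- Relative: 7.849 × (0.2499 + 0.2465) / 0.049² = 1,623; × 1.5 = 2,434.
- 10 points: 7.849 × (0.2499 + 0.2379) / 0.10² = 383; × 1.5 = 574.

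| Variant, 80% power, design effect 1.5 | Relative | 10 points |
|---|---|---|
| Two-sided, unpooled | 2,434 | 574 |
| Two-sided, pooled | 1,626 × 1.5 = 2,439 | 386 × 1.5 = 579 |
| Two-sided, continuity-corrected | 2,501 | 609 |
| One-sided, pooled | 1,922 | 456 |

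None is near 3,200. Inputs that the protocol does not state come close on the relative reading: a design effect of 2.0 (1,626 × 2 = 3,252) or 90% power (2,176 × 1.5 = 3,264).

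For a comparison of two rates the discrepancy is on the large side: 3,200 / 2,439 = 1.31, and 3,200 per group gives about 89% power on the relative reading.

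**2. The double difference.** Take cell rates of 49%, 49%, 49% and 44.1% (or 39%), that is, no change in the control arm, with the design effect of 1.5 applied in every cell. The cell is one arm at one survey.

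- Relative: 7.849 × (3 × 0.2499 + 0.2465) / 0.049² × 1.5 = about 4,885 per cell.
- 10 points: 7.849 × (3 × 0.2499 + 0.2379) / 0.10² × 1.5 = about 1,163 per cell.

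Power with 3,200 per cell, relative reading: SE = √(0.9962 × 1.5 / 3,200) = 0.0216; Φ(0.049/0.0216 − 1.96) = about 0.62.

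| Scenario | Power, relative | Power, 10 points |
|---|---|---|
| 3,200 children per cell, design effect 1.5 | 62% | 99.6% |
| 3,520 children per cell, design effect 1.5 | 66% | 99.8% |
| 3,200 per cell, clustering cancels fully (design effect 1, assumed) | 79% | above 99% |
| 3,200 participants per cell, 80% children (assumed) | 53% | 98.6% |
| 3,200 participants per cell, half children (assumed) | 36% | 91% |
| 1,600 children per cell (3,200 covers both arms or both surveys) | 36% | 91% |

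Detectable double difference at 80% power and design effect 1.5: 2.80 × 0.0216 = about 6 points at 3,200 per cell, and about 8.5 points at 1,600.

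**The case against.** The strongest reply is that the discrepancy is harmless: for the comparison that the inputs describe, 3,200 is more than enough on either reading. That stands, so the failure to reproduce 3,200 does not by itself show an undersized survey.

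Four stronger conclusions are tempting and go beyond the text.

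- **That 62% is an upper limit on power.** It is one scenario. Partial cancellation of clustering is plausible, because Study site places control areas in the same 29 union councils as the intervention areas and both surveys cover that territory. The wording also permits the 10-point reading, although 3,200 would then be about 5.5 times its own requirement (3,200 / 579).
- **That the formula is certainly a two-group one.** The formula is not shown. The conclusion rests on the listed inputs, which contain no control-group change. Doubling the two-sample number for a double difference while leaving out the design effect also gives 3,252 (1,626 × 2), but that would drop an input that the section states.
- **That the 3,200 definitely includes women.** The sentence lists who is studied in the selected households. 7,040 from 4,200 households is about 1.7 per household, which could be children alone. The text does not settle it, and the child shares used above are assumptions.
- **That the loss of power carries into the cost-effectiveness analysis.** That analysis uses a before-and-after effect, which is the contrast that p1 and p2 describe.

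The survey is also not the only evidence of impact, since the nested cluster trial is sized separately. What remains is that the sample size, its inputs and the double difference do not agree within the protocol's own text, so this is not detail that can simply be left to an analysis plan.

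**Conclusion.** The point holds. As written, the sample size and its inputs contradict each other: 3,200 is stated where the inputs give about 2,434 to 2,501 (relative) or 574 to 609 (10 points). The inputs size a before-after or two-group contrast, while the study-design section plans a double difference.

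For the double difference, the claimed 80% power is not supported on the relative reading. It is about 62% if all 3,200 are children in each arm at each survey and the design effect of 1.5 applies in full. It is still just under 80% if clustering cancels completely, and it is lower if women are counted or if 3,200 spans both arms or both surveys. On the 10-point reading the number is ample. The protocol does not say which reading applies, so the defect is an unsupported power statement and not a proven shortage of participants.

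**What to change.** In the survey sample-size section:

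1. Give p2 as a number and say whether the 10% is relative or absolute.
2. Correct either the 3,200 or the inputs so that one follows from the other.
3. State which contrast is primary, and reconcile Methodology and Study Design, the text under Figure 1 and Cost Effectiveness Analysis.
4. Define the sizing unit as children under five with a valid height-for-age z-score, per arm per survey.
5. Restate the power or the detectable difference for the double difference at the actual number of children, with the design effect assumed for it. The 6 and 8.5 points worked out above are illustrations that hold only for 3,200 and 1,600 children per arm per survey at a design effect of 1.5.

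The cost is one recalculation and a change of wording, with no extra enrolment. The downside is that the stated power may become less favourable.

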**Data Analysis**

For data analysis SPSS version 18 will be used and data will be analysed using univariate and multivariate methods. Statistical Analysis will be performed after the availability of clean and quality data. Each file will be converted from Fox Pro into SPSS files so that they could be read into SPSS for further analysis. Descriptive statistics for the subjects will be obtained and Pearson Chi square test will be used to establish association between categorical variables. Simple frequency tables will be generated to ascertain the information on Socio-economic and demographic data. Bivariate analysis will be done to establish association with the various factors and growth parameters such as stunting, wasting and underweight. Data analysis will be conducted based on the agreed dummy tables.

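### The survey's covered and uncovered areas come from the same 29 union councils, but the only test named estimates no double difference and uses neither the clustering nor the match

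*Protocol*

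**What the plan says.** Under Study site, the LHW catchment areas of the 29 UCs form the intervention group, "while remaining uncovered area of these union councils will be in control group". Under Methodology and Study Design, the impact design is a double difference: "We propose to compare the intervention and non-intervention (control) groups before (first difference) and after the intervention (second difference"). Fresh random samples are drawn in both kinds of area at baseline and at endline.

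The survey sample-size section considers "80% power to detect 10% reduction in prevalence of stunting" "with a significance level of 0.05 was considered for sample size estimation", starting from 49%, with this entry for clustering: "DEFF : The estimated design effect = 1.5". These are inputs for two independent proportions, and no term for matching is listed. The section adds that "LHW catchment areas of 29 UCs will be treated as a cluster for intervention group and control group", under two-stage sampling.

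The Data Analysis section states that "Pearson Chi square test will be used to establish association between categorical variables". It also mentions bivariate analysis, unspecified univariate and multivariate methods, and agreed dummy tables. No section pairs, stratifies or adjusts by UC.

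**The concern.** Each UC can supply its own control at both rounds. Whatever the two parts of a UC have in common, including an event between rounds that hits both, cancels in a within-UC double difference. The named test cannot make use of this. A two-group chi-square compares two proportions at one time, takes every respondent as independent, and does not know which UC a respondent came from.

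The double difference is the protocol's programme-level answer on stunting, so its standard error matters. If clustering is ignored, the standard error is too small wherever the two parts of a UC are not perfectly alike, and the test rejects too often. If clustering is allowed for but the match is not, the standard error is too large and the test is conservative.

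**Working it through.** **The plan's own figure.** For two proportions at two-sided 0.05 and 80% power, 49% against 44.1% (a relative 10% fall) needs 1,626 per group, and 1,626 x 1.5 = 2,439. For 49% against 39% (10 points) the result is 386 x 1.5 = 579. Neither is the stated 3,200. That is a separate matter, and 3,200 is taken as given below.

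**Inputs from the protocol.** K = 29 UCs; 3,200 per group; p = 0.49; design effect 1.5. Per UC, arm and round, m = 3,200/29 = 110.

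**Intra-cluster correlation (ICC).** The survey section gives none.
- From its design effect: (1.5 - 1)/(110 - 1) = 0.0046.
- The only ICC in the protocol, 0.02, belongs to the nested trial's child cohorts. For the survey it would mean a design effect of 1 + 109 x 0.02 = 3.18, so it is an assumption here.

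**Share s.** The fraction of between-area variance common to both parts of a UC is not in the protocol. It is varied from 0 to 80%, split equally between a lasting UC effect and a UC-by-round shock.

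**Formulas.** With equal cells the estimate is the same under all three analyses; only the standard error used differs.
- True (and paired) variance: (4p(1-p)/K) x [ICC(1-s) + (1-ICC)/m]
- Variance assumed if the 116 cells are treated as independent clusters (112 df): the same with s = 0
- Variance assumed under simple random sampling: 4p(1-p)/(Km)

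Here 4 x 0.49 x 0.51/29 = 0.03447. The simple-random-sampling SE is sqrt(0.03447/110) = 1.77 points. The unpaired cluster SE is 2.17 points at ICC 0.0046 and 3.16 at 0.02.

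False-positive rate with simple-random-sampling errors = 2 x Phi(-1.96 x 1.77/true SE). At ICC 0.0046 and s = 0 this is 2 x Phi(-1.96 x 1.77/2.17) = 11%. Unpaired power = Phi((effect - 1.98 x unpaired SE)/true SE). Paired power uses the noncentral t with 28 df.

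| ICC | Share s | True SE (points) | False positives, simple-random-sampling errors | False positives, unpaired cluster | Power at 4.9 points, unpaired / paired |
|---|---|---|---|---|---|
| 0.0046 | 0% | 2.17 | 11.0% | 4.8% | 61 / 59% |
| 0.0046 | 25% | 2.08 | 9.5% | 3.8% | 61 / 63% |
| 0.0046 | 50% | 1.98 | 7.9% | 3.0% | 62 / 67% |
| 0.0046 | 80% | 1.85 | 6.1% | 2.0% | 63 / 72% |
| 0.02 | 0% | 3.16 | 27.2% | 4.8% | 33 / 32% |
| 0.02 | 25% | 2.87 | 22.7% | 2.9% | 32 / 38% |
| 0.02 | 50% | 2.55 | 17.4% | 1.4% | 30 / 46% |
| 0.02 | 80% | 2.11 | 10.0% | 0.3% | 26 / 61% |

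Simulation of the same set-up gives a change in power from pairing of about -3 to +9 points at ICC 0.0046 and -1 to +34 at 0.02. It agrees with the table to about one point.

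**A 10-point fall.** At ICC 0.0046 both analyses exceed 99%. At 0.02, simulated unpaired and paired power are 88/87%, 90/92%, 93/96% and 96/99.7% as s rises, a gain of at most about 4 points.

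**The case against.** A reader might infer that the named test itself costs up to 34 points of power. It does not. With simple-random-sampling errors the double difference rejects 68-76% of the time at 4.9 points (ICC 0.02), more than the paired test's 32-62%, because its error rate is inflated. The power loss belongs to a cluster-adjusted analysis that ignores the match, which the protocol nowhere proposes. That comparator also throws away the matching across rounds. At ICC 0.02 and 80% shared, power is 27% for that comparator, 42% when each area is differenced across rounds but arms are left unpaired, and 62% with full pairing. Nearly half of the largest figure is therefore not due to arm pairing. The figure also needs an ICC that contradicts the survey's own design effect. This objection stands, and the size of the point is stated accordingly.

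A reader might also infer that the sample size is wrong because it omits the match. Leaving out a positive match overstates the number needed, so it is safe on this ground.

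The pairing is not fully explicit. The sample-size section calls LHW catchment areas the clusters. The protocol involves more than 500 LHWs, and the number of first-stage units is not given. That all 29 UCs enter both arms at both rounds is the natural reading of Study site, but it remains a reading. The 3,200 participants also include women, so the number of children per cell may be below 110.

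Finally, an analysis plan may exist, and multivariate methods leave room for UC terms. That is fair: nothing excludes a suitable model. But the protocol has its own Data Analysis section, and the one test it names does not estimate the effect its design section defines.

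**Conclusion.** The point holds as a mismatch between the stated design and the stated analysis. The design is a double difference with both arms in the same UCs. The named test estimates no double difference and uses neither the clustering nor the match.

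The firmer consequence is a false-positive rate above 5% if simple-random-sampling errors are used: about 6-11% at the survey's own design effect and about 10-28% at ICC 0.02. The gain from pairing over an unmatched cluster analysis is secondary and conditional. For a 4.9-point fall it is modest at the stated design effect and can be large only at the higher ICC with much shared variance. For a 10-point fall it hardly matters. The protocol does not say whether its 10% reduction is relative or absolute, so both cases are shown.

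All figures rest on 29 complete pairs, equal cells of 110 and an assumed share of 0-80%. A further worry is that UC-specific events such as floods would bias a pooled contrast. That follows only if the UCs carry different weights in the two arms. Annex I, which holds the covered and uncovered populations, is not shown, so the documents do not establish it.

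**What to change.** In the Data Analysis section, state that the survey effect on stunting is estimated as a within-UC double difference, by one of two methods:

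- compute the double difference for each UC and test the mean with a one-sample t-test (28 df if all 29 UCs contribute); or
- fit an individual-level model with arm, UC-by-round fixed effects and the arm-by-round term, with standard errors clustered by UC.

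State that a UC with only a covered or only an uncovered part does not enter the contrast. Chi-square can stay for descriptive tables.

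The cost is wording, provided UC is recorded for each household. If the two parts of a UC share nothing, pairing loses about 1-3 points of power, and any one-arm UC is lost. No change to the sample size is needed on this ground.
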